## Abstract

Nearly 90% of diarrhea-related mortalities are the result of unsafe drinking water, poor sanitation, and insufficient hygiene. Although “Water, Sanitation, and Hygiene” (WASH) interventions may significantly reduce the risk of diarrheal disease, it is currently unclear which interventions are the most effective. In this study, we aim to determine the importance of contextualizing a WASH intervention to the local context and the needs for increasing impact (Clinicaltrials.gov NCT03709368). A total of 1500 households in rural Tanzania will participate in this cluster randomized controlled trial. Households will be randomized into one of three cohorts: (1) a control group receiving a basic intervention and 1 placebo household visit, (2) an intervention group receiving a basic intervention + 9 additional household visits which are contextualized to the setting using the RANAS approach, and (3) an intervention group receiving a basic intervention + 9 additional household visits, which are not contextualized, i.e., a general intervention. Assessments will take place at a baseline, 1 and 2 years after the start of the intervention, and 1 year after the completion of the intervention. Measurements involve questionnaires and spot checks. The primary outcome is hand-washing behavior, secondary objectives include, the impact on latrine use, health, WASH infrastructure, quality of life, and cost-effectiveness.

## 1. Introduction

Diarrhea is ubiquitous among people in low-and middle-income countries (LMIC) [1]. Each year, approximately 1.7 billion children globally are faced with diarrheal disease. Children under five years of age are particularly vulnerable, with 525,000 mortalities per year [2]. Unsafe drinking water, poor sanitation, and insufficient hygiene are responsible for nearly 90% of these mortalities [3,4,5].

“Water, Sanitation, and Hygiene” (WASH) interventions were demonstrated to significantly reduce the risk of diarrheal disease [6]. Hand-washing with water and soap, in particular, is shown to significantly reduce the microbial load of the hands [7] and was shown to reduce the risk of diarrhea with 39–47% [6,7,8,9,10]. Despite its enormous health impacts, only 5–25% of people in LMIC are estimated to wash their hands with water and soap after fecal contact [10,11]. In a Cochrane systematic review by Ejemot-Nwadiaro et al., attempts to change either hygiene practices [12], hand-washing at critical times [13], or soap consumption [14] only led to modest improvements [9].

Several studies have suggested that multifaceted interventions, including both hardware (i.e., improvement of infrastructure) and software (i.e., improvement of knowledge, skills, and attitude), are needed to obtain lasting behavioral changes [15,16,17]. In addition, contextualizing the interventions and ensuring that the program is tailored to the needs of the participants may further increase impact [16]. Despite the many reports that have been published in recent years, a recent mixed methods systematic review by De Buck et al. showed that there is no consensus as to the most efficacious approach in improving WASH behavior in LMIC [18]. The systematic review also showed that contextualized hand-washing interventions using the ‘Risks, Attitudes, Norms, Abilities, Self-regulation’ (RANAS) model— a theoretical framework which can be used to tailor the content of the intervention to the context at play—show great promise for ameliorating behavior [18]. Indeed, RANAS trials were published to be successful in improving water [19,20,21], sanitation [22,23], and hygiene [24,25,26] behavior in various settings around the world. However, these trials made use of a low-quality, uncontrolled before-after study design, and largely focused on short-term behavior change, while long-term changes have gone uninvestigated. Moreover, the effects on health tend to be insignificant. With this study, we want to determine whether multifaceted contextualized interventions, based on the RANAS model versus non-contextualized WASH interventions have a differential impact on behavior and related health outcomes. The evidence regarding the efficacy of WASH interventions is not ideal, particularly as large RCTs are needed, which do not assist in determining long-term effects.

The primary objective of this study is to determine the effectiveness of add-on contextualized and non-contextualized interventions on hand-washing behavior at critical times. As a secondary objective, the study aims to evaluate the impact on latrine use, health, quality of life and hardware coverage. It will also calculate the cost-effectiveness of each approach.

## 2. Materials and Methods

To draft the protocol, we made use of the reporting criteria provided in the SPIRIT checklist (Supplementary Table S1).

### 2.1. Design

This study is a prospective, parallel group, single blinded, cRCT with a 2 year implementation period and a 12 month follow-up. It is a collaboration between Belgian Red Cross (BRC), Tanzania Red Cross Society (TRCS), and the Environmental and Occupational Health Department of Muhimbili University of Health and Allied Sciences (MUHAS).

Participants will be randomized to one of three cohorts: A contextualized intervention cohort, a non-contextualized intervention cohort, or a control cohort. A contextualized intervention is defined as an intervention that is adapted to the local context by collecting data at baseline and using this data to fit the intervention to the specific population needs, as prescribed by the RANAS approach. In contrast, a non-contextualized intervention is a general WASH intervention that is not fine-tuned to meet the specific needs of the context at hand. For the purpose of this study, the target population will be subdivided into three cohorts: (1) a control cohort receiving a basic intervention + 1 placebo household visit, (2) a contextualized intervention cohort receiving a basic intervention + 9 household visits which are contextualized to the setting using the RANAS approach, and (3) a non-contextualized intervention cohort receiving a basic intervention + 9 household visits which are not contextualized, i.e., a general intervention. The study flow chart can be found in Figure 1.

### 2.3. Sample Size Calculation

The primary outcome of the study is the prevalence of hand-washing after defecation or latrine using. This prevalence will be compared between intervention and control groups at post-intervention. Since we have an interest in comparing both interventions groups separately, the alpha-level will be set at 0.025 (0.05/2).

The sample size estimate was based on the literature and earlier pilot work, which assumed that 5% of the households wash their hands after defecation, at a baseline, and a 15% improvement is expected following contextualized and non-contextualized interventions. To detect an increase in hand-washing prevalence after defecation or latrine using 5% to 20%, 92 households are needed per group to have 80% power, based on a two-sided Chi-square test (α = 0.025). However, the drop-out rate and intra-cluster correlation (ICC) still need to be taken into account. The ICC refers here to the potential correlation in the probability of hand-washing between the households of the same sub-village. The inflation in sample size due to the ICC is given by 1 + ICC*(*m −* 1), where *m* equals the mean number of households per sub-village. 

With 500 households per group (clustered in 9 sub-villages), including a drop-out rate of 20%, the variance inflation factor should be maximal 4.35 (400/92), corresponding to an ICC of 0.076 (4.35 = 1 + 0.076 × (45 − 1)). This closely corresponds to the most conservative estimate found in literature for a comparable outcome [27,28,29]. The calculation is also conservative, since the analysis will be based on a longitudinal statistical model, including data from earlier time points for drop-out participants and the baseline measurement will be used as a covariate. These further increases the power of the study. In conclusion, a total sample of 1500 households were included, i.e., 500 households per cohort. A detailed overview can be found in Table 1.

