### 2.8. Data Analysis

Statistical analyses will be undertaken using R studio (Version 1.0.143). All analyses will be conducted on an intention-to-treat principle using all randomized participants. Demographic characteristics and baseline data will be summarized by descriptive statistics using means, standard deviations and 95% confidence intervals for continuous variables, median and inter-quartile ranges for non-normal continuous or ordinal data and percentages for categorical data. The primary and secondary outcome measures will be analyzed using generalized linear mixed models with baseline values as a covariate to assess differences between treatment groups and across time. A sensitivity analysis will be performed comparing effectiveness of the interventions in low compliance versus high compliance households. All data will be adjusted for multiple comparisons. A *p*-value < 0.05 will be considered as statistically significant.

Investigators who are involved in data analysis will be blinded to group allocation. In accordance to the European General Data Protection Regulation (GDPR) law, all private information (i.e., name or GPS) will not appear on any documents except a participant key. This key is needed to match baseline data with midline, end-line, and follow-up data. A pseudonym will be used to protect participants’ identities. The key linking the participant name to the data is not accessible to the investigators and will be destroyed after data analysis is complete.

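### Testing the two add-on cohorts by Holm's step-down instead of at a fixed 0.025 each would raise power at the same 5% family-wise error: a cheap efficiency gain, not a correction of an error

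*Protocol article*

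**What the plan says.** Section 2.3 defines the primary comparison: "This prevalence will be compared between intervention and control groups at post-intervention". It gives the reason for splitting the error rate, "Since we have an interest in comparing both interventions groups separately", and then the rule: "the alpha-level will be set at 0.025 (0.05/2"). The size follows from it: "92 households are needed per group to have 80% power, based on a two-sided Chi-square test (α = 0.025"). The assumed control rate is "5% of the households wash their hands after defecation, at a baseline", and the assumed effect covers both add-ons: "a 15% improvement is expected following contextualized and non-contextualized interventions". Nothing in 2.3 mentions a step-down, an ordering of the hypotheses or the reuse of error rate after a rejection.

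Section 2.8 says "All data will be adjusted for multiple comparisons" and takes p < 0.05 as significant. It names no adjustment method and does not refer back to 0.025.

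**The concern.** The only multiplicity rule the article states for the primary comparisons is an equal, single-step split of 0.05. Once one add-on has been shown superior at 0.025, a family-wise 5% budget allows the other to be tested at the full 0.05. A fixed split does not use that allowance.

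The planning scenario expects a 15-point improvement in both add-on cohorts, so both null hypotheses are assumed false, and that is a setting in which a step-down helps. At stake is the second claim: whether the trial can say that both kinds of household visit, and not just one, improve hand-washing over control.

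**Working it through.** **Inputs, all from section 2.3.** Control 5%; each add-on cohort 20%; two-sided 0.025 per comparison; 80% power; 500 households per cohort, 400 after 20% drop-out; variance inflation 4.35; hence 400/4.35 ≈ 92 effective households per arm.

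**Step 1: reproduce the plan's figure.** Pooled two-proportion formula without continuity correction:

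n = [z(0.9875)·√(2·p̄·(1−p̄)) + z(0.80)·√(p₁(1−p₁) + p₂(1−p₂))]² / (p₂−p₁)²

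with p̄ = 0.125:

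- √(2 × 0.125 × 0.875) = 0.4677
- √(0.0475 + 0.16) = 0.4555
- n = (2.2414 × 0.4677 + 0.8416 × 0.4555)² / 0.0225 = 91.1, rounded up to 92

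This matches. So do 400/92 = 4.35 and (4.35 − 1)/44 = 0.076.

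**Step 2: power at 92 for one comparison.**

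- At 0.025: Φ[(0.15·√92 − 2.2414 × 0.4677)/0.4555] = Φ(0.857) = 80.4%
- At 0.05: Φ[(0.15·√92 − 1.9600 × 0.4677)/0.4555] = Φ(1.146) = 87.4%

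The first is the fixed split. The second is what no adjustment at all would give, so it is a ceiling.

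**Step 3: error control of Holm.** If both nulls are true, a false rejection requires at least one p ≤ 0.025, with probability at most 0.025 + 0.025 = 0.05. If one null is true, it can be rejected only with p ≤ 0.05. Neither statement uses the correlation from the shared control.

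**Step 4: compare the two rules.** The two z statistics share the control arm. Under 5%/20%/20% their correlation is 0.0475/0.2075 = 0.23. Results come from 2,000,000 normal draws at 92 effective households per arm:

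| True rates (control / add-on / add-on) | Quantity | Fixed 0.025 | Holm |
|---|---|---|---|
| 5 / 20 / 20 | each comparison | 80.4% | 85.6% |
| | both | 66.6% | 77.0% |
| | at least one | 94.3% | 94.3% |
| 5 / 20 / 15 | stronger add-on | 80.5% | 83.3% |
| | weaker add-on | 50.8% | 59.7% |
| | both | 43.6% | 55.4% |
| 5 / 20 / 5 | effective add-on | 80.5% | 80.6% |
| | null add-on (false rejection) | 2.5% | 4.4% |
| 5 / 5 / 5 | family-wise error | 4.6% | 4.6% |

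(The first entry is the Step 2 value; the simulation gives 80.5%.)

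**Step 5: consistency check.** P(first) + P(second) = P(at least one) + P(both). Holm leaves P(at least one) unchanged, so its gain for both must equal the sum of the two single gains. For 20/20 that is 5.2 + 5.2 = 10.4 points, which agrees with 77.0 − 66.6 = 10.4.

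**Step 6: binomial data instead of normal.** At 5/20/20, each comparison goes from 83.2% to 87.7%, both from 72.9% to 81.9%, and at least one is 93.6% under either rule. Levels shift, but the ordering does not.

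**The case against.** The strongest reply is that the article does not clearly fix Bonferroni for the analysis. The 0.025 stands in the sample-size section, and an adjusted p-value set against 0.05, as in 2.8, is compatible with Holm. A condensed article may also leave the choice of procedure to an analysis plan. This stands in part. It is why the point cannot be called an error, and why the remedy is an added sentence in 2.8. It does not remove the point: 2.3 states a concrete rule in the future tense, and no other rule appears.

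A second reply is that the gain is not wholly free. Bonferroni decisions agree with 97.5% confidence intervals and Holm decisions need not. With p = 0.03 in the second comparison, Holm may declare an effect while the 97.5% interval includes no effect. This is a legitimate reason for preferring the split, and it stands as a cost to disclose.

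Several stronger readings are tempting, and the document does not support them:

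- *That an add-on with p between 0.025 and 0.05 will be reported as having no effect.* No section says so, and 2.8 calls p < 0.05 significant. The fair statement is that the two thresholds are not reconciled.
- *That both add-ons at 20% is where the split loses most.* The gain for both is 11.8 points at 20%/15% and about 12.0 at 17%/17%, against 10.4 at 20%/20%.
- *That under Holm the stated 80% becomes a guaranteed floor.* If only one add-on works, Holm adds almost nothing. With a t reference on 24 degrees of freedom, power for that comparison is about 75% under either rule.
- *That the trial has no power to spare.* Section 2.3 describes its ICC as close to the most conservative literature estimate and expects unquantified gains from the longitudinal model and baseline covariate.

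Finally, naming Holm for two tests does not decide which tests form the family. The Introduction and Conclusions also express interest in contextualized versus non-contextualized, and 2.7.1 repeats the analysis for each critical time. That question stays open.

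**Conclusion.** The plan's split is valid, and its 92, 4.35 and 0.076 are correct. Holm is uniformly at least as powerful at the same family-wise 5%. On the plan's own figures it adds about 5 points of power per comparison (80.4% to 85.6%) and about 10 points for showing both effects (66.6% to 77.0%). It does not change the chance of at least one success, and it gains almost nothing if only one add-on works.

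The sizes rest on the stated rates, equal effective samples of 92 per arm and a normal approximation. A mixed model with nine sub-villages per arm would shift the absolute powers but not the ordering of the rules. This is an inexpensive efficiency improvement, not a mistake in the plan.

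**What to change.** Leave 0.025 in the sample-size calculation of 2.3; it is Holm's first step, so the sizing stays valid. Add to 2.8, before unblinding:

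> The two comparisons of add-on cohorts with control for hand-washing after defecation or latrine use at post-intervention are tested by Holm's procedure at family-wise two-sided 0.05 (smaller p against 0.025; if significant, the other against 0.05).

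This gives the unnamed adjustment a method for the primary family and reconciles the 0.025 of 2.3 with the 0.05 of 2.8. If 97.5% intervals are reported for both contrasts, add a line saying that such an interval may include no effect for a comparison Holm declares significant.

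The cost is two sentences, with no extra households, visits or data. The timing matters: adopted after results are known by arm, the same change would look opportunistic.

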### 2.5. Description of the Interventions

The intervention was subdivided into a basic intervention, which provides all cohorts equally, and add-on household visits, which differ from one cohort to another. All interventions will be delivered by TRCS volunteers, who received formal training prior to implementation. Participants and TRCS volunteers were not blinded for the intervention status. 

#### 2.5.1. Basic Intervention

The basic intervention involves both hardware and software components. Hardware interventions are aimed at improving the infrastructure: An existing water gravity flow scheme will be rehabilitated and extended, 350 tippy taps and 350 pans for pour flush latrines will be distributed, and sanitation blocks will be built in four schools. In addition, community sessions will be provided to each of the sub-villages (*n* = 27), teaching participants how to build a tippy tap, how to build an improved latrine, and how to make liquid soap.

Software interventions involve the improvement of knowledge, skills, and attitude. In order to reach this goal, Community-Led Total Sanitation (CLTS), Participatory Hygiene and Sanitation Transformation (PHAST), and School Water, Sanitation and Hygiene (SWASH) clubs will be used. CLTS sanitation and hand-washing sessions will follow the National Guidelines for Rural Community Led Total Sanitation (R-CLTS) [31], and UNICEF material [32]. In brief, a 1 h meeting will take place in each of the villages involving community leaders and locals to familiarize them with the intervention, and to ensure optimal co-operation during implementation. Then, two community sessions with a duration of 3–5 h each will be organized in each of the sub-villages separately (*n* = 27). A first session will focus on sanitation [31], and a second session will focus on hand-washing [32]. Finally, a series of follow-up community meetings and household visits will take place to monitor improvement. PHAST sessions are based on a manual from the World Health Organization [33]. Considering the overlap with some CLTS activities, only a selection of the full guideline will be enrolled, namely: (1) Health problems in our community, (2) Good and bad hygiene behaviors, (3) Investigating community practices, (4) How diseases spread, (5) Blocking the spread of disease, (6) Selecting the barriers, (7) Choosing sanitation improvements, and (8) Choosing improved hygiene behaviors. These 8 activities will be enrolled in approximately 40 community groups, which are spread out over the sub-villages. Each activity will take between 30 min–2 h to complete.

#### 2.5.2. Add-On Intervention

All cohorts will receive an add-on intervention on top of the basic intervention package. The content of this add-on intervention will differ from one cohort to another.

##### Contextualized Intervention Cohort

The contextualized intervention cohort will receive nine household visits of 20–40 min each, at a frequency of one visit every two months. The content of these add-on visits is based on the ‘Risks, Attitudes, Norms, Abilities, Self-regulation’ (RANAS) model (www.ranasmosler.com) [16]. The RANAS model consists of five behavioral factors, which are considered to be the drivers of WASH behavior [16] (see Figure 2). In a preparatory phase, RANAS dictates that questionnaires and interviews are used to better understand the context at play, i.e., do people in the intervention area wash their hands and why (not)? In a second phase, this data is used to develop the intervention, thus optimally tailoring the program to the needs in the community [16,34].

Concretely, baseline data are first gathered through a questionnaire (Table S2). Then, these data will be analyzed to compare (1) people who always wash hands after defecation (do’ers) to people who don’t (non-do’ers); and (2) people who always use the latrine (do’ers) to people who do not (non-do’ers). Do’ers were defined as people who always wash their hands or use the latrine. Non-do’ers were defined as people who wash their hands or use the latrine most of the time, sometimes, seldom or never. Only those behavioral factors (i.e., ‘Risks, Attitudes, Norms, Abilities, and/or Self-Regulation’), that are significantly different between “do’ers” and “non-do’ers” will be included in the intervention, as these are, at least theoretically, considered to be decisive for hand-washing and latrine use behavior in the current setting [16,34]. This implies that the precise content of the intervention can only be determined after baseline data collection has taken place.

##### Non-Contextualized Intervention

The non-contextualized intervention cohort will also receive nine household visits of 20–40 min each, at a frequency of one visit every two months. The content of these visits involves a general WASH intervention which is not tailored to the context at hand. Based on a study by Mosler et al., who suggested that norms are a universal driver (i.e., not context specific) of hand-washing behavior [35] and other studies and expert input stating that norms of local leaders, in particular, are important in African culture in inducing behavioral change [36,37,38], the focus would be non-contextualized intervention on norms. Concretely, the ‘Norm Behavior Change Techniques’ from the RANAS manual (www.ranasmosler.com) were used to outline the intervention [16]. These interventions encourage participants to improve their hand-washing and sanitation infrastructure and behavior in order to become a WASH role model within their community. A detailed outline of the non-contextualized intervention can be found in Table S3.

##### Control

The control cohort will receive one household visit of 20–40 min. During this visit, a placebo poster will be distributed focusing on malaria nets. The main goal of this household visit is to avoid jealousy among the control cohort.

### 2.6. Assessment Protocol

A repeated measures design will be employed with assessments performed at baseline (May 2018), after one year (May 2019) and after two years (May 2020) of intervention, and at 1 year of follow-up, i.e., one year after the intervention has stopped (May 2021) (Figure 2). All assessments will be performed by trained assessors who are not involved in the implementation of the interventions, and who are blinded to group allocation. Assessments will take place at about the same time of year to avoid variability of performance due to the rainy season.

All data will be collected by means of KoboToolbox (https://www.kobotoolbox.org/), or on paper (EQ-5D-3L + informed consent). Moreover, collected data are checked daily during data collection by means of a computer script (R studio), to ensure that no mistakes have taken place – i.e., doubles in the dataset.

